## Introduction

Colorectal cancer (CRC) is one of the most common malignancies in western countries. In 2018, about half a million cases were diagnosed in Europe, and 250,000 of those affected died due to this disease [1]. Most of the CRCs diagnosed are candidates for surgical resection with curative intent. Cure rates after surgery vary from 92% to 67% depending on the tumor stage [2]. However, colorectal surgery is associated with some life-threatening complications. There are several risk factors associated with these postoperative complications: age, sex, comorbidities, surgery urgency, tumor location, type of surgical approach, and surgical and hospital volume. Postoperative complications are detected during admission in 30% to 40% of patients who have had colorectal surgery [3-6]. Further, one study reported a lower percentage in the month after discharge (15%) and in the first year after surgery (25%) than at other times [3]. The most common complications are anastomotic failure, intra-abdominal infection, prolonged ileus, surgical site infection, deep vein thrombosis, pulmonary complications, and cardiac complications [6]. To assess the severity of surgical complications, different scales are available but the Clavien-Dindo classification is the most used in all parts of the world [7].

Some interventions have been proposed to reduce complications associated with colorectal surgery. Preoperative intravenous antibiotic prophylaxis is commonly used for the prevention of infectious postoperative complications [8]. The most appropriate regimen for antimicrobial prophylaxis for colorectal procedures and the optimal choice of antimicrobial agent have not been fully resolved. However, the last consensus international guidelines on antimicrobial prophylaxis recommend agents with activity against the anaerobic and aerobic floras of the bowel administered within 60 minutes before surgical incision [9]. Studies have shown that oral antibiotic administration can also reduce the risk of infections associated with surgery [10,11]. Other studies, however, have shown that this type of intervention does not modify the mortality and severity of other complications detected [12,13].

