#### Blood Samples

Blood samples will be collected at baseline and closeout visits. These samples will be stored at –20 ℃ until analysis. Laboratory analysis will include hemoglobin, mean corpuscular volume, mean corpuscular hemoglobin, albumin, prealbumin, C-reactive protein, creatinine, prothrombin time, neutrophil-lymphocyte ratio, IL-6, IL-10, and TNF-α levels.

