#### Inferential Statistics

We will apply inferential statistics to identify differences between the control and experimental groups. In general, dichotomous variables will be compared with chi-square tests, whereas qualitative variables with more than 2 categories will be compared with analysis of variance tests. Continuous variables will be compared with *t* tests for independent samples or Mann-Whitney *U* tests if they do not meet normality. *P*<.05 will be considered statistically significant. More specifically, to analyze the outcomes of the study the following statistical methodology will be performed:

We will analyze the complication rate after surgery in the 2 intervention groups. We will base this analysis on severity and type of complication. After stratification by tumor location, we will use chi-square tests to identify significant differences between the 2 groups. Risk ratio and 95% confidence interval will be used to describe the differences found.We will describe adverse events reported in each group. To find significant differences between the 2 groups, chi-square tests will be used after stratification by tumor location. Risk ratio and 95% confidence interval will be used to describe the differences found.Diversity and composition of the gut microbiota will be analyzed in the 2 groups using McNemar tests and *t* tests to identify significant differences between the groups.Inflammatory differences between the 2 intervention groups will be analyzed with *t* tests if variables meet normality or Wilcoxon tests if variables do not meet normality. We will also analyze the dynamic changes of the neutrophil-lymphocyte ratio in the 2 intervention groups.Differences in dietary pattern and quality of life will be analyzed with McNemar tests for qualitative variables and *t* tests for quantitative data.We will perform a univariate analysis to identify any associations between impact of the microbiome, inflammatory and dietary patterns, and surgery complications. We will perform a multivariate regression with the significant variables found. In addition, the model fit will be assessed using a likelihood-ratio test, area under the receiver operating characteristic curve, Akaike information criterion, and Bayesian information criterion, and we will then validate the model designed using the bootstrap method.

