Finally, we will perform a causal mediation analysis to measure the direct and indirect effects of Micodigest 2.0 on colorectal surgery complications. We will include as mediators the variables related to complications after surgery. This analysis will also show the total effect of other variables on colorectal surgery complications.

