## Discussion

### Principal Findings

The trial has been designed to evaluate the effects of a new dietary supplement on complications associated with surgery in CRC patients. The results, if positive, may provide a change in the current guidelines for preoperative care in CRC. Additionally, this study protocol will confirm the safety of the Micodigest 2.0 supplement and evaluate patient adherence to this new treatment. In sum, the results may provide a simple, safe, and inexpensive intervention with good adherence rates to reduce surgery complications and consequently improve the quality of life of CRC patients.

The protocol is necessary not only to study the effects of Micodigest 2.0 but also to investigate patterns and features related to complications after surgery. The results may show clinical features, inflammatory patterns, or nutritional statuses associated with postoperative complications. Moreover, the results could show new effects of gut microbiota on surgery complications. Therefore, the protocol could identify risk factors for postoperative complications and contribute to the design of new clinical studies to prevent CRC surgery complications.

Interest in the role of fungal polysaccharides in gut microbiota and immune regulation has increased in recent years. The results of this study may improve the knowledge about the biological functions of fungal polysaccharides. Further, this trial may help to define new health benefits of these bioactive polysaccharides and design new studies on their use in CRC patients. Hence, the use of fungal polysaccharides as probiotics could introduce a new step in the prevention and treatment of CRC. Bioactive polysaccharides may improve the response to treatment, especially immunotherapies, due to their immunomodulating activity. These polysaccharides could also increase the safety of treatments commonly used in cancer and alleviate adverse effects of these therapies. Additionally, the anti-inflammatory activity of fungal polysaccharides could influence carcinogenesis, progression, and tumor metastasis.

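### The regression of complications on microbiome, inflammatory and dietary markers omits treatment arm and the known clinical risk factors, so a marker with no effect can be credited with theirs

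*Protocol article*

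**What the plan says.** Under Inferential Statistics the protocol article sets out two steps for the secondary objective on how markers affect complications. The screen: "We will perform a univariate analysis to identify any associations between impact of the microbiome, inflammatory and dietary patterns, and surgery complications". The model: "We will perform a multivariate regression with the significant variables found". The general rule in the same section is that P<.05 "will be considered statistically significant". Fit statistics and bootstrap validation follow.

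Treatment arm is not named in either step. Tumor location is used for the arm comparison ("After stratification by tumor location, we will use chi-square tests to identify significant differences between the 2 groups") but is not mentioned for the regression. The Introduction says: "There are several risk factors associated with these postoperative complications: age, sex, comorbidities, surgery urgency, tumor location, type of surgical approach", and adds surgical and hospital volume. None of these is named for the regression.

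Markers are measured twice: "Blood samples will be collected at baseline and closeout visits", and stool likewise. The regression does not say which measurement enters.

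A causal mediation analysis comes next: "We will include as mediators the variables related to complications after surgery". The Discussion says that "the protocol could identify risk factors for postoperative complications".

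**The concern.** The secondary objective is worded as an effect of the markers, and the Discussion speaks of risk factors. A confounded association does not support either.

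The trial's own hypotheses make arm a common cause. The product is expected to change the microbiome, inflammation and nutrition, and the sample size assumes that it halves complications. If both are true and the arms are pooled, any closeout or change value moved by the product is associated with complications, whether or not it matters biologically. The active capsules contain two named bacterial species that the placebo lacks, and stool is sequenced at closeout, so a taxon that merely shows who took the product is a realistic candidate.

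The second route does not depend on the product. Albumin, hemoglobin or C-reactive protein may track age or comorbidity, and would then carry those factors' association with complications at baseline as well as at closeout.

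The planned fit statistics and bootstrap address fit and optimism. They do not detect confounding.

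**Working it through.** **Inputs from the article (Sample Size).** Control complication rate 40%, a 50% reduction (so 20%), 64 per arm before dropout, 10% dropout, 144 in total.

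**The plan's figure.** With pooled variance and no continuity correction, n = [z(.95)·√(2×.30×.70) + z(.80)·√(.40×.60 + .20×.80)]² / .20² = (1.645×.648 + .842×.632)² / .04 ≈ 63.9, so 64 per arm. 64/.90 = 71.1, so 72 per arm and 144 in total. This reproduces the figure one-sided; a two-sided test gives 82. That is a separate matter and nothing below depends on it. Expected complications among 128 evaluable patients: 64×.40 + 64×.20 = 38.4.

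**Route 1: arm, closeout or change values.** Take a taxon with no effect, detected in a share a of active and b of placebo patients (assumed). With equal arms:

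- P(complication | present) = (.20a + .40b)/(a + b)
- P(complication | absent) = (.20(1−a) + .40(1−b))/(2 − a − b)

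For 80% v 20%: (.16 + .08)/1 = .24 and (.04 + .32)/1 = .36, so the odds ratio is (.24/.76)/(.36/.64) = 0.56. The other rows follow in the same way. The last two columns are simulated shares of trials with P<.05, 64 per arm: pooled chi-square, and Mantel-Haenszel stratified by arm.

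| Detected, active v placebo | Complications, present v absent | Pooled odds ratio | Without arm | Given arm |
|---|---|---|---|---|
| 60% v 40% | .28 v .32 | 0.83 | 8% | about 5% |
| 60% v 30% | .267 v .327 | 0.75 | 11% | about 5% |
| 80% v 20% | .24 v .36 | 0.56 | 32% | about 5% |
| 90% v 10% | .22 v .38 | 0.46 | 52% | about 5% |

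For an inert continuous marker (logistic regression, 128 patients, 3000 runs per scenario), the screen fires in 9.2%, 12.9%, 19.4% and 30.4% of runs for assumed shifts of 0.5, 0.8, 1.0 and 1.5 SD. With arm in the model it fires in 4.4% to 5.1%.

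**Route 2: an omitted risk factor, any time point.** The marker is inert and unaffected by the product, but has assumed correlation r with a risk factor of assumed odds ratio per SD.

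| r | Odds ratio per SD | Unadjusted | Arm only | Arm and risk factor |
|---|---|---|---|---|
| 0.3 | 1.5 | 8.2% | 8.6% | 5.4% |
| 0.3 | 2.0 | 15.1% | 15.6% | 5.0% |
| 0.5 | 1.5 | 15.7% | 16.1% | 4.6% |
| 0.5 | 2.0 | 34.5% | 36.0% | 4.6% |

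**Both routes in opposite directions** (0.8 SD shift; r = 0.3, odds ratio 2): 5.2% unadjusted, 14.3% with arm only, 4.6% with both. The two biases can cancel, and adjusting for arm alone can then uncover the other.

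**Price of adjustment.** With equal arms, arm and taxon correlate at about 0.6 (80/20) and 0.8 (90/10). Standard errors grow by roughly 1/√(1−.36) = 1.25 and 1/√(1−.64) = 1.67. For a taxon that carries the whole product effect, simulated power falls from about 99% to 93% at 80/20 and from about 88% to 47% at 90/10.

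**The case against.** The strongest reply has four parts.

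**The list may be condensed.** The article does not call its candidate list exhaustive, the Discussion expects findings on clinical features, and covariates of a secondary model are often left to an analysis plan. This stands only in part. The article gives both a candidate list and an entry rule, and a plan that followed them would leave arm and the risk factors out.

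**Confounding is conditional.** A reader might infer that every marker will be falsely credited. The article does not support that. By randomization, baseline values are independent of arm, so route 1 needs closeout or change values and a marker that the product moves. With modest shifts the excess is small (8% at 60% v 40%). Large shifts are plausible for the two dosed bacteria but are not documented for any marker. All of this stands.

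**The mediation analysis involves arm.** A reader might infer that the error passes straight into it. Because that analysis separates direct from indirect effects of the product, an inert marker moved only by arm should show an indirect effect near zero. What remains is that the analysis names no confounders of mediator and outcome, and that it does not correct the regression reported for the marker objective.

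**The setting narrows the risk factors.** One hospital removes hospital volume as a confounder, and restriction to ASA I or II narrows comorbidity. Age, sex, tumor location and the remaining ASA difference are still there.

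**Conclusion.** The point holds in conditional form. Followed as written, the regression can give a confounded answer to the marker objective: by arm if closeout or change values are used, and by clinical risk factors at either time point. At the planned rates and 64 per arm, false selection of an inert taxon through arm ranges from about 8% to 52% across the assumed detection rates, against about 5% given arm. Through an omitted risk factor it ranges from about 8% to 35% across the assumed correlations and odds ratios. The article supplies none of those shifts, correlations or odds ratios, so the ranges show what is possible and are not forecasts.

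Two further readings go too far. Adding arm alone would not be sufficient, because it leaves risk-factor confounding in place. And the primary comparison of complication rates is not in doubt: it rests on randomization and does not use this model. The change should be made, but it concerns a secondary analysis.

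**What to change.** In Inferential Statistics:

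- State whether baseline, closeout or change values of the markers enter the regression.
- Force tumor location, age, sex and ASA class into both the marker-by-marker screen and the multivariable model whatever their P values. Add treatment arm for closeout or change values.
- Report marker effects conditional on these terms.
- Use penalised (Firth) logistic regression. With about 38 expected events, five forced terms plus one marker leave 38.4/6 = 6.4 events per term, so the set should stay short and be fixed in advance.
- Use the same baseline covariates in the mediator and outcome models of the mediation analysis.

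No new data are needed: arm and tumor location are known at randomization, ASA class is an eligibility item, and demographics are collected at the first visit. The cost is up to five degrees of freedom, wider intervals, and the loss of power shown above for a true mediator closely tied to arm. The plan should acknowledge that loss, so that a null result for such a marker is not read as evidence of no effect.

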### Randomization

We will randomize into the 2 parallel treatment arms using the distribution of a blinded treatment kit containing test or placebo supplementation. We will perform randomization using a code list randomly created using R software (R Foundation for Statistical Computing). This code list will include a total of 144 random numbers. Each random number will match with a unique identification code that will identify test or placebo. The randomization will ensure an equal sample size for each group. The dietary supplement will be randomly assigned into the test or placebo groups at a 1:1 ratio according to the random numbers generated.

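### The mediation analysis of Micodigest 2.0 is said to show the total effect of other variables as well; as described, it estimates effects of the randomised product only

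*Protocol article*

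**What the plan says.** The last paragraph of Inferential Statistics in the Protocol article names one exposure: "we will perform a causal mediation analysis to measure the direct and indirect effects of Micodigest 2.0 on colorectal surgery complications". It defines the mediators by their relation to the outcome: "We will include as mediators the variables related to complications after surgery". It closes with the sentence at issue: "This analysis will also show the total effect of other variables on colorectal surgery complications". The other variables are not listed, and neither the outcome model nor its covariates are given.

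Three other places bear on the point.

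- Under Randomization, only the supplement is allocated by chance: "The dietary supplement will be randomly assigned into the test or placebo groups at a 1:1 ratio".
- Earlier in Inferential Statistics, risk factors have an analysis of their own: "We will perform a univariate analysis to identify any associations between impact of the microbiome, inflammatory and dietary patterns, and surgery complications", followed by "We will perform a multivariate regression with the significant variables found".
- The Discussion (Principal Findings) states what the results are for: "Therefore, the protocol could identify risk factors for postoperative complications and contribute to the design of new clinical studies to prevent CRC surgery complications".

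**The concern.** A mediation analysis takes one exposure and splits its total effect into a part that runs through the mediators and a part that does not. Here the exposure is the product. Nothing in that calculation produces a total effect for a different variable. The coefficient of another variable in the outcome model is its association with complications at fixed arm and fixed mediators. That differs from a total effect in two situations:

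- **The variable acts through a mediator.** Holding the mediator fixed removes that part of its effect. Nutrition, blood and fecal measures are taken at both baseline and closeout, so a baseline measure acting through a closeout marker is quite possible here.
- **The mediator and complications share an unmeasured cause.** Conditioning on the mediator can then link a variable to complications although it has no effect on them.

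Apart from both, the other variables are observed and not randomised, so a causal reading needs assumptions about confounding that randomisation does not supply. At stake is the fourth secondary objective, the effect of microbiome, inflammation and nutrition on complications. A reader who took the closing sentence at face value could dismiss a real upstream cause, or carry a spurious one into the design of a new prevention study.

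**Working it through.** **No figure to reproduce.** The sentence carries no number. From Sample Size I use only 64 evaluable patients per arm and the 40% control rate with a 50% reduction, that is 20%. Expected events are 0.40 × 64 + 0.20 × 64 = 25.6 + 12.8 = 38.4, about 38 among 128 patients.

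**Model.** All effect sizes below are assumptions; the documents give none. X is the 1:1 randomised arm, C a non-randomised baseline variable, M a mediator, U an unmeasured variable and Y a complication. C and U are standard normal.

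- M = −0.5·X + m·C + u·U + e, with e standard normal
- logit P(Y = 1) = −0.6 − 0.3·X + d·C + b·M + v·U

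Two linear-probability models are compared: Y on X and C (total effect of C), and Y on X, C and M (the mediation outcome model). Coefficients come from a sample of 1,000,000. Rejection rates at P<.05 come from 2,000 trials of 128 patients.

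| Case | d, m, b, u, v | C without M | C given M | Rejected without M | Rejected given M |
|---|---|---|---|---|---|
| (a) C acts only through M | 0, 0.7, 0.6, 0, 0 | 0.081 | 0.000 | 52% | 4.5% |
| (b) partly through M | 0.3, 0.7, 0.6, 0, 0 | 0.133 | 0.056 | 91% | 20% |
| (c) wholly outside M | 0.4, 0, 0.6, 0, 0 | 0.076 | 0.076 | 45% | 47% |
| (d) no effect; M and Y share U | 0, 0.7, 0, 0.7, 0.7 | −0.001 | −0.047 | 4.5% | 16% |
| (e) opposing paths | −0.4, 0.7, 0.6, 0, 0 | 0.004 | −0.077 | 5% | 38% |

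Cases (a) and (b) lose a real effect, (d) creates a false one, (e) reports a clear effect where the total is close to zero, and (c) shows no distortion.

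**Does summing the paths repair it?** In linear models the total is the coefficient given M plus m times the coefficient of M (0.115, 0.110, 0.066 and 0.117 in a, b, d and e):

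- (a) 0.000 + 0.7 × 0.115 = 0.081
- (b) 0.056 + 0.7 × 0.110 = 0.133
- (d) −0.047 + 0.7 × 0.066 = −0.001
- (e) −0.077 + 0.7 × 0.117 = 0.005, against 0.004 (rounding)

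So the sum recovers the value without M in every case, including (d). A path model that reported these sums for C would avoid the distortion. It would still be open to confounding of C with Y, since C is not randomised.

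**How far the size depends on the inputs.** A second simulation used logistic models and standardised variables, again with 128 patients.

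- *Full mediation.* With correlation 0.5 between variable and mediator and a mediator odds ratio of 2 per SD, detection was 37.6% without the mediator and 4.5% with it. At correlation 0.7 and odds ratio 3 it was 92.3% and 5.7%. At correlation 0.3 and odds ratio 1.5 it was only about 10% and 5%.
- *No effect, shared cause.* False rejection given the mediator was 57.3% at correlations of 0.6 and odds ratio 3, 14.7% at 0.5 and 2, 7.5% at 0.4 and 2, and about 6% at 0.3 and 2.

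**The case against.** The strongest reply is that the article names no outcome model. Total effect, in path analysis, means direct plus indirect, and the sums above show that this reading escapes the distortion. That stands: the rejection rates apply only if the effects of other variables are read from the mediator-conditional model. It does not rescue the sentence. The analysis described has one exposure, and path totals for other variables would be a further analysis, still observational.

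A second reply is that the other variables may be the mediators themselves. For a single mediator, or the last in a chain, nothing downstream is held fixed, so the first mechanism does not apply. That also stands, and confounding remains there too.

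Third, a condensed article may leave model detail to a full protocol or analysis plan. True, and the absence of that detail is not the point here. The point is a sentence that assigns to a stated analysis a quantity it does not deliver.

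A reader might infer more: that the trial will reach wrong conclusions on risk factors. The documents do not support that. Objective 4 has its own univariate and multivariable regression, whose univariate step holds no mediator fixed. The Discussion speaks of features associated with complications and says only that "the protocol could identify risk factors for postoperative complications". It does not tie this to the mediation output. Case (c) shows that some variables would be unaffected.

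**Conclusion.** The concern holds in a limited form. The closing sentence attributes to the mediation analysis a causal quantity that the analysis, as described, does not estimate. Reading other variables' coefficients as total effects could hide upstream causes or produce false associations. The size ranges from almost nothing to a near-complete loss of detection, or to false-positive rates far above 5%. Where it falls depends on effect sizes that the documents do not give, on whether a variable acts through a mediator or shares in mediator–outcome confounding, and on the model used. With path sums, only confounding is left. The issue is confined to a secondary, exploratory analysis.

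**What to change.** Delete the closing sentence of the mediation paragraph, or limit it to the total, direct and indirect effects of Micodigest 2.0. Address objective 4 through the regression already planned in Inferential Statistics, with three conditions:

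1. Do not adjust a baseline variable for closeout markers that lie downstream of it.
2. Keep the covariate list short, given about 38 expected events. A separate, heavily adjusted model for every microbiome feature would not be workable.
3. Report the results as observational associations, not total effects.

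The cost is one sentence and some care in specifying a regression on data that will be collected anyway. The price is a more modest claim for the variables that are not randomised.
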